# 7.0 Procedures and Methods:

## 7.1 Procedures:

The following procedures will be done at the indicated times (see also Appendix B: IDB-13005 Time and Events Tables B.1 and B.2).

### 7.1.1 First Screening Visit (days - 150 to - 7):

 Written, witnessed informed consent for screening will be obtained.

- A brief medical history will be obtained to ensure that the subject meets historical criteria for enrollment, and approximately 10 mL of blood will be drawn for A/Panama/2007/99 serum HAI antibody screening determination (see section 7.2).

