| Investigational Product: | FluINsure Proteosome Trivalent Influenza Vaccine:  Form: liquid (**0.9** mL per 3 mL vial)  Dose: either 15 μg or 30 μg of each of three (3) influenza hemagglutinins complexed to proteosomes, total volume administered will be 0.28 mL by nasal spray  Route: Intranasal  Lot number: 1066  Each vial contains:   1. 150  30 g / mL of hemagglutinin (HA) from *each* of A/New Caledonia/20/99 (H1N1), A/Panama/2007/99 (H3N2) and B/Shangdong/7/97 viruses, non-covalently bound to outer membrane proteins (OMP) of *Neisseria meningitidis* strain 8047 (OMP to HA ratio is approximately 4:1). 2. 10 mM Na/K phosphate-buffered isotonic saline, pH 7.4, with 0.01% thimerosal 3. Non-hemagglutinin viral proteins 4. Trace amounts of egg proteins |
| Control Product: | Phosphate buffered normal saline diluent / placebo:  Form: liquid (10 mL per 20 mL vial)  Dose volume: 0.28 mL by nasal spray  Each vial contains:  10 mM Na/K phosphate-buffered isotonic saline, pH 7.4, with 0.01% thimerosal |
| Challenge: | A/Panama/2007/99, lot I B 44/3, prepared in eggs in compliance with GMP, sterile and mycoplasma-free |
| Trial Time Lines: | Screening in March 2003. Immunization in June 2003. Challenge July 2003. |

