## 4.2 Inclusion Criteria:

To be eligible for study, each subject will fulfill all of the following criteria:

 Age 18 to 50 years, inclusive,

 Comprehension of the study requirements, including willingness to forego the licensed 2003-2004 intramuscular influenza vaccine until completion of study participation; availability for the required study period, ability to attend scheduled study visits, and willingness to participate in the inpatient challenge,

- Willingness to provide written consent for participation after reading the Consent Form and after having adequate opportunity to discuss the study with an investigator or qualified deputy,
- Good general health status as determined by a screening evaluation no greater than 90 days prior to the first immunization,
- For female subjects, provision of a history of reliable contraceptive practices (hysterectomy or bilateral tubal ligation, oral or implanted contraceptive use, intrauterine device, barrier method plus spermicide, history of a single male partner with vasectomy, or a history of abstinence deemed credible by the investigator). *The provision of this history does NOT replace the requirement to perform, and obtain negative results in, pregnancy tests as per sections 4.3 and 7.2.5.*
- Reciprocaltiter of serum hemagglutination-inhibiting (HAI) antibody to A/Panama/2007/99 (H3N2) ≤ 10.

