## 5.1 Immunization Phase:

FluINsure™ will be delivered as one of three different treatment regimens as detailed below in section 5.1.1. In addition, approximately one of every four subjects will receive a placebo control treatment regimen comprising two sequential doses of buffered saline placebo.

The study will enroll up to 112 healthy adult subjects selected for susceptibility to A/Panama/2007/99 into the immunization component.

Healthy normal subjects of both genders and 18 to 50 y.o. will be invited to give informed consent for preliminary screening phlebotomy, and then have a serum specimen obtained for baseline A/Panama/2007/99 HAI antibody testing. Screened subjects with serum reciprocal HAI titers ≤ 10 will be invited to return for a detailed explanation of the clinical trial and asked to give informed consent for participation in the trial itself. Consenting subjects will then undergo an assessment of their medical history, physical examination, ECG, and selected clinical laboratory tests to ensure eligibility according to the protocol. A nasal wash sample for measurement of secretory IgA (nasal sIgA) specific for the vaccine virus strains will be obtained during screening.

5.1.1 Treatments:

Eligible subjects will be randomized, using a gender-specific randomisation list prepared by the Sponsor, to one of four treatment groups in a ratio of approximately 1:1:1:1. The treatment groups will receive:

Treatment Group A) Two intranasal spray doses, each dose containing 15 μg of each of three hemagglutinins (HA) formulated with proteosomes. The first dose will be given on day 0 and the second given after a 14-day interval.

Treatment Group B) Two intranasal spray doses, the first containing 30 μg of each of three hemagglutinins (HA) formulated with proteosomes, and the second containing buffered saline (placebo). The first dose will be given on day 0 and the second given after a 14-day interval.

Treatment Group C) Two intranasal spray doses, each containing 30 μg of each of three hemagglutinins (HA) formulated with proteosomes. The first dose will be given on day 0 and the second given after a 14-day interval.

Treatment Group D) Two intranasal spray doses of buffered saline. The first dose will be given on day 0 and the second given after a 14-day interval.

All dose volumes will be 0.28 mL (as 0.14 mL per nostril). Each treatment group will include approximately 28 subjects.

5.1.2 Safety and Tolerability Evaluation:

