### 7.1.3 Immunization Phase Day 0, First Treatment:

 Subjects’ eligibility for enrollment based on ECG and clinical laboratory data from the prior screening visit will be reviewed.

 An interval medical history will be performed to ensure that each subject continues to meet all inclusion and no exclusion criteria.

- A urine specimen will be collected from each female subject and tested in the clinic for evidence of pregnancy. No test article will be administered until a negative result is obtained and documented.
- A directed examination of the ears, cervical lymph nodes, and nasopharynx will be done, the results of which will be recorded using the worksheet provided as Appendix C.
- Each subject will be interviewed regarding the presence of baseline upper respiratory complaints and / or symptoms of systemic illness prior to dosing, using a “Memory Aid” format consistent with that presented in Appendix D.
- Volunteers with any grade 2 physical findings or grade 2 symptoms among their baseline Memory Aid observations will not be given a test article dose. Such volunteers may return at a later time point and be considered for enrollment if findings/symptoms resolve.
- Approximately 30 mL of venous blood will be obtained for baseline *in vitro* cytokine stimulation studies and HAI antibody titers.
- Test article will be administered intranasally as described in section 6.5. (*Subjects who receive any amount of test article will be considered enrolled and followed for safety and immunogenicity through the Challenge Phase Day 20 -30 visit as specified below and in section 8.0 (regardless of whether the subject receives further test article or is challenged). No additional follow-up will be required of subjects who are screened but do not receive any test article*.)

 Subjects will be observed for thirty (30) minutes after dosing. At the end of this interval, each subject will have a repeat oral temperature measured and recorded and complete a questionnaire eliciting immediate post-immunization symptoms (present at the time of observation or in the preceding 30 minutes). Each will be graded as: none, mild (just noticeable), moderate (unpleasant/uncomfortable, but not incapacitating), or severe (preventing resumption of normal activities). The questionnaire is provided as Appendix E.

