- A  4-fold increase in serum A/Panama/2007/99 HAI antibody titer between day 39 ( 3) and the final follow-up visit, and absent clinical disease suggesting influenza between discharge from the isolation unit and the final follow-up visit.

9.3.7 Laboratory-confirmed Influenza Illness:

A subject will be deemed to have laboratory-confirmed influenza illness if he/she meets the definitions for BOTH of:

- Influenza infection, and
- Illness (Any).

9.3.8 Analysis:

9.3.8.1 Power Considerations:

The analysis will consider both binary outcomes (e.g., illness vs. no illness; virus shedding vs. no virus shedding, etc.) and continuous outcomes (e.g., treatment group mean temperatures, tissue counts, peak viral shedding and shedding AUC, etc.). The variability, and potential magnitudes of the differences in the latter are *a priori* unknown. However, the virus challenge inoculum will be selected to yield *approximately* 50 - 60%, based on past experience, of the binary outcome “any illness.” (Closer control of this rate is difficult to ensure.) Assuming that a minimal efficacy level of 70% (where efficacy = [rate controls -ratetreated ] x 100 / rate controls) is of interest to justify further development of a given dose or formulation, it is possible to calculate that a group size of 28 will yield ≥ 0.80 power to detect a ≥ 70% reduction in the rate of the binary outcome “any illness.”

9.3.8.2 Analyses:

The analysis concerns between-group comparisons of the four cross-over groups regarding clinical and immunologic binary outcomes. Alternative definitions provide six binary clinical outcomes (fever, upper respiratory illness, lower respiratory illness, systemic illness, illness [any], and illness + infection) that can be compared between groups by chi-square tests. More flexible analyses use logistic regression (SAS PROC LOGISTIC) with the presence or absence of influenza, separately for each definition, as the outcome. Covariates are cross-over study group, age, gender, race, and, for some models, titers after vaccinations 1 and 2.

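### Susceptibility rests on a screening HAI titre up to 150 days old, and the Day 0 pre-dose titre is not among the covariates listed for the challenge outcomes

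*Protocol*

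**What the plan says.** - **Criterion.** Protocol 4.2 requires a reciprocal titre of serum HAI "antibody to A/Panama/2007/99 (H3N2) ≤ 10". It sets no limit on the age of that titre, although the general-health evaluation in the same list must fall within 90 days of the first dose.
- **When it is applied.** Under 5.1, "Screened subjects with serum reciprocal HAI titers ≤ 10 will be invited to return". The sample is the one taken at 7.1.1, headed "First Screening Visit (days - 150 to - 7". The synopsis timeline reads "Screening in March 2003. Immunization in June 2003. Challenge July 2003".
- **Day 0.** Section 7.1.3 states that "Subjects’ eligibility for enrollment based on ECG and clinical laboratory data from the prior screening visit will be reviewed". It also calls for an interval history to confirm that all entry criteria are still met. At the same visit, "Approximately 30 mL of venous blood will be obtained for baseline" cytokine studies and HAI titres. Section 7.2.6 has this sample tested against all three strains. No step makes dosing, continued eligibility or challenge depend on the result.
- **Challenge admission.** Section 7.1.10 sets the HAI criterion aside, on the ground that immunisation has made it irrelevant.
- **Efficacy models.** Section 9.3.8.2 states: "Covariates are cross-over study group, age, gender, race, and, for some models, titers after vaccinations 1 and 2". Baseline titre is used in the immunogenicity models of 9.1 but is not listed here.

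**The concern.** Objective C is protection of adults who were susceptible beforehand, and the HAI titre is the only measurement that selects them. A subject exposed to an H3N2 virus between the screening sample and Day 0 could be randomised, challenged and analysed as susceptible without being so. Section 1.0 calls A/Panama the current A/H3N2 strain, so exposure is conceivable, though the protocol does not say that it circulates in those months.

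A subject who cannot become ill carries no information on protection. In the placebo arm such subjects lower the control attack rate that the inoculum is chosen to produce, and the power statement depends on that rate. With about 25 challenged per arm, one or two falling unevenly also add noise to the efficacy estimate.

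The choice of covariates makes this harder to handle. The list includes titres that vaccination itself changes and leaves out the one titre it cannot change. A pre-dose value is a legitimate adjustment variable and can define a subset without breaking the randomised comparison. A post-vaccination titre can do neither for the total vaccine effect.

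**Working it through.** **1. Age of the qualifying titre.** From 31 March to 1 June 2003 is 62 days; from 1 March to 30 June is 121 days. The visit window allows 150.

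**2. The plan's own power figure.** Inputs from 9.3.8.1 and 9.0: 28 per group, placebo any-illness rate p of 50% to 60%, efficacy 70% (vaccine rate 0.3p), two-sided 5%. With the normal approximation for two proportions, power is 0.816 at p = 0.50 (0.50 v 0.15) and 0.919 at p = 0.60 (0.60 v 0.18). The stated figure of at least 0.80 reproduces.

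**3. Starting point at the challenged number.** Section 4.1 expects about 25 challenged per group, and 9.0 makes the chi-square tests exact. With 25 per group, Fisher's exact test gives 0.676, 0.760 and 0.834 at p = 0.50, 0.55 and 0.60. The shortfall at the lower rates is a separate matter and does not come from non-susceptible subjects.

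**4. Dilution.** Let f be the share of each arm no longer susceptible at Day 0 and assume those subjects do not become ill. The protocol gives no value for f, so the range is an assumption. The rates become p(1 − f) and 0.3p(1 − f). Expected efficacy is 1 − 0.3p(1 − f) / [p(1 − f)] = 70% for every f that is equal across arms. Only power changes:

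| f | Placebo rate at p = 0.55 | Fisher, 25 per arm, p = 0.50 | p = 0.55 | p = 0.60 | Normal approx., 28 per arm, p = 0.50 | p = 0.60 |
|---|---|---|---|---|---|---|
| 0 | 0.550 | 0.676 | 0.760 | 0.834 | 0.816 | 0.919 |
| 5% | 0.523 | 0.631 | 0.715 | 0.792 | 0.784 | 0.893 |
| 10% | 0.495 | 0.587 | 0.667 | 0.744 | 0.749 | 0.863 |
| 20% | 0.440 | 0.502 | 0.569 | 0.640 | 0.674 | 0.791 |

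On the plan's own method and 28 per arm, f = 5% takes power below 0.80 at a 50% placebo rate. At 60%, power stays above 0.80 until f is a little under 20%.

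**5. Chance imbalance.** Take two independent binomial counts with 25 per arm and f = 10%. The arms differ by at least 2 such subjects with probability 0.47 and by at least 3 with probability 0.23. The effect on the estimate is modest:
- Two such subjects in the placebo arm only: 0.55 × 23/25 = 0.506, and 1 − 0.165/0.506 = 67%.
- Two in a vaccine arm only: 0.165 × 23/25 = 0.152, and 1 − 0.152/0.55 = 72%.

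For scale, the approximate 95% interval around 70% efficacy with 25 per arm uses a log-risk-ratio standard error of √[0.45/(25 × 0.55) + 0.835/(25 × 0.165)] = 0.485. It runs from 22% to 88%.

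**The case against.** A reader might infer that subjects already immune are in fact challenged and that their staying well is wrongly credited to the vaccine. The documents support neither step. No infection or seroconversion rate for the interval is given, so their presence is only a possibility. Allocation is randomised 1:1:1:1 with placebo, so such subjects are expected equally in every arm and leave expected efficacy unchanged. The imbalance examples move efficacy by two to three points in either direction, well inside the sampling error.

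Other points on that side:
- **Interval history.** The Day 0 review is not confined to ECG and laboratory data; an interval history checks the entry criteria again. It could pick up a recent influenza-like illness. It cannot establish a titre, and nothing makes dosing wait for the Day 0 result.
- **Double counting.** The planned placebo rate comes from past experience, and 5.2 aims the inoculum at a rate in placebo recipients as enrolled. Some non-susceptible subjects may already be in that rate. This stands: the power losses above are upper values for a given f.
- **Choice of cut-off.** Section 1.0 treats titres below 40 as typically susceptible. Making Day 0 HAI of 10 or less the main efficacy population would drop subjects whom the protocol's own background still regards as susceptible. This stands, and confines the restriction to a sensitivity analysis.
- **A matter for the SAP.** Analysis sets often are. But 9.3.8.2 names its covariates and includes titres, so what it lists can be judged as written.
- **Possible use elsewhere.** The later analysis relating HAI to viral load gives no time point, so it cannot be said that the Day 0 titre is never used against challenge outcomes. The point is limited to the listed covariates and comparisons.

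**Conclusion.** The point holds in a limited form. One screening titre, up to 150 days old and about 62 to 121 days old on the stated calendar, fixes susceptibility. The pre-dose titre that could update it is collected, but it is not among the listed covariates for the challenge outcomes, while post-vaccination titres are.

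The likely consequence is some loss of attack rate, power and precision, without bias in expected efficacy. The size cannot be stated from the documents. The table shows what an assumed 5% to 20% would do if those subjects never become ill, are equally frequent across arms and are not already counted in the planned placebo rate. This is a worthwhile improvement at almost no cost; it is not a flaw that invalidates the efficacy comparison.

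**What to change.** In 9.3.8.2 and the matching synopsis text:

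1. Add log10 Day 0 (pre-dose) A/Panama HAI as a covariate in the logistic models of illness and the linear models of shedding, including those without post-vaccination titres. State the value assigned to titres below the lowest dilution.
2. Keep all challenged subjects as the main comparison.
3. Pre-specify a sensitivity analysis of illness and shedding in subjects whose Day 0 A/Panama HAI is 10 or less, the protocol's own entry criterion. Report by arm how many are excluded, which would also show how large the problem was.

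The cost is wording. The sample and assay are already planned, and no visit, dosing step or challenge eligibility rule changes. The sensitivity analysis will have slightly smaller arms. The logistic models gain one parameter against few events: at 55% placebo illness and 70% efficacy in all three vaccine arms, about 25 × 0.55 + 3 × 25 × 0.165 = 26 illnesses in total. If nearly all Day 0 titres are still 10 or less, the adjustment will change little, and that result would itself answer the question. The change should be made before unblinding, since the same analysis chosen later would look post hoc.

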### 7.1.2 Second Screening Visit (days -90 to - 5):

- This visit will occur within the above interval, but not prior to completion of A/Panama/2007/99 HAI determination on the “first screening” specimen.
- Subjects’ eligibility for enrollment based on history and HAI data will be reviewed.
- A detailed explanation of the clinical trial will be provided to subjects remaining eligible, and **written informed consent** to trial participation will be elicited.
- Vital signs and a complete baseline physical examination will be performed and recorded.
- An ECG will be performed.
- Approximately 25 mL of blood will be drawn and a urine specimen obtained for baseline clinical laboratory tests, **drug screening,** and HIV serologies (see section 7.2).
- A nasal wash specimen for specific influenza antibody assay will be obtained (section 7.2).

### 7.1.3 Immunization Phase Day 0, First Treatment:

 Subjects’ eligibility for enrollment based on ECG and clinical laboratory data from the prior screening visit will be reviewed.

 An interval medical history will be performed to ensure that each subject continues to meet all inclusion and no exclusion criteria.

- A urine specimen will be collected from each female subject and tested in the clinic for evidence of pregnancy. No test article will be administered until a negative result is obtained and documented.
- A directed examination of the ears, cervical lymph nodes, and nasopharynx will be done, the results of which will be recorded using the worksheet provided as Appendix C.
- Each subject will be interviewed regarding the presence of baseline upper respiratory complaints and / or symptoms of systemic illness prior to dosing, using a “Memory Aid” format consistent with that presented in Appendix D.
- Volunteers with any grade 2 physical findings or grade 2 symptoms among their baseline Memory Aid observations will not be given a test article dose. Such volunteers may return at a later time point and be considered for enrollment if findings/symptoms resolve.
- Approximately 30 mL of venous blood will be obtained for baseline *in vitro* cytokine stimulation studies and HAI antibody titers.
- Test article will be administered intranasally as described in section 6.5. (*Subjects who receive any amount of test article will be considered enrolled and followed for safety and immunogenicity through the Challenge Phase Day 20 -30 visit as specified below and in section 8.0 (regardless of whether the subject receives further test article or is challenged). No additional follow-up will be required of subjects who are screened but do not receive any test article*.)

 Subjects will be observed for thirty (30) minutes after dosing. At the end of this interval, each subject will have a repeat oral temperature measured and recorded and complete a questionnaire eliciting immediate post-immunization symptoms (present at the time of observation or in the preceding 30 minutes). Each will be graded as: none, mild (just noticeable), moderate (unpleasant/uncomfortable, but not incapacitating), or severe (preventing resumption of normal activities). The questionnaire is provided as Appendix E.

- Each subject will be provided with a Memory Aid (Appendix D) and a digital thermometer and instructed to take his/her temperature and complete a Memory Aid page each evening from Day 0 to Day 6. Subjects will be instructed to notify the clinic (Retroscreen) should they experience grade 2 or greater symptoms, and to return as instructed for physician evaluation.
- Subjects will be instructed to return to the clinic (Retroscreen) on Day 7, with their Memory Aid

### 7.1.4 Immunization Phase Days 0 – 6 (0 to 6 days after the First Treatment)

- Subjects will maintain their Memory Aids and measure evening temperatures daily.
- Subjects will report any grade 2 or greater symptoms, or fever (oral temperature ≥ 37.9º C) to study site personnel, who will arrange for a physician evaluation.
- Physician evaluations will be performed as needed, and recorded in a uniform manner utilizing the worksheet provided as Appendix C.

### 7.1.5 Immunization Phase Day 7 ( 1 day, Follow-up Visit One):

 Vital signs will be taken and recorded.

 Each subject’s Memory Aid will be reviewed, collected, and the data abstracted and recorded. Subjects who have lost their Memory Aids will be provided with new documents, which will be completed from memory with the assistance of the interviewer. Such data will be clearly annotated as RETROSPECTIVE.

 Subjects will be queried regarding the occurrence of adverse events not specified in the Memory Aid, and any new concomitant medications taken, and the results recorded.

 A brief, directed examination of the ears, cervical lymph nodes, and naso-pharynx will be performed to detect objective signs of vaccine-induced reactogenicity. The examiner will complete the brief exam worksheet provided as Appendix C.

 Subjects will be given an appointment to return to the clinic on Immunization Phase Day 14  2.

